### Adverse events

Therapists will inquire about adverse events at the start of each treatment day. Adverse events will also be monitored at all post-assessments and followed up by the research team until they have abated or until a stable situation has been reached.

A substantial protocol modification will be notified to the Medical Ethics Review Board through an amendment. Only on approval will we make modifications and upload the new protocol version to the registry (Clinicaltrials.gov and Research with Human Participants). Modifications will then be communicated to relevant parties, such as participants, trial therapists and other researchers.

On expressing willingness to participate, the patient will provide written informed consent in twofold based on the Centrale Commissie Mensgebonden Onderzoek (CCMO) approved format (see online supplemental appendix A – in Dutch), which includes an opt-out option for data use for other research, data storage outside the EU and collecting biological hair samples.

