### Study design and procedures

#### M-TFT protocol

The M-TFT protocol is a comprehensive treatment approach designed to address PTSD through a structured series of sessions. Participants engage in two preparatory sessions once per week, lasting 50 min each, focusing on psychoeducation and case conceptualisation. In the third week, the core treatment starts, consisting of 5 days of M-TFT delivered over 1 week or 2 weeks. Each M-TFT day features a 60-minute PE therapy session, a break and a 60 min EMDR session. The sequencing of PE followed by EMDR has been demonstrated to be more effective than the reverse order.^18^ Two 50-minute closing sessions, one in week 5 and one in week 6, consist of summarising learnt information and preventing relapse. To enhance feasibility, therapist rotation may be incorporated into the treatment plan, which has been found to have no negative effects on the therapeutic relationship.^19^ The total treatment duration for M-TFT is 800 min over 5–6 weeks.

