#### S-TFT protocol

The S-TFT protocol comprises either 12 weekly 60-minute sessions plus a last 80-minute session (13 total sessions) or 16 weekly 50-minute sessions, both amounting to a total treatment duration of 800 min. This variable session structure was chosen in order to align with the existing financial reimbursement structures of the participating treatment sites. The S-TFT protocol consists of evidence-based first-line treatment interventions according to the Dutch treatment guideline for PTSD,^8^ which include PE, EMDR therapy, BEPP, NET and ImRs. Although different trauma-focused interventions are applied, they share core elements, including psychoeducation, imaginal exposure, emotional processing, cognitive restructuring and/or meaning-making.^20^ This condition therefore strongly resembles standard clinical care in the Netherlands. The S-TFT protocol does not include therapist rotation.

Both treatment conditions will be conducted face to face at five outpatient treatment centres specialising in psychotrauma in the Netherlands: ARQ Centrum’45, ARQ IVP, Psy-Zo!, Psychotraumacentrum Haarlem and the Military Mental Health Care.

We increase treatment fidelity through several measures. Study therapists must be licensed psychologists or be supervised by one. For all treatment interventions, certified and specific training in each modality is required. Also, therapists are required to follow a mandatory 2.5-day certified training on massed trauma treatment, covering the latest developments in the treatment interventions used in the study. Supervision with a frequency of once every 3 weeks for M-TFT and once every 6 weeks for S-TFT is provided to address treatment progress and problems. Furthermore, audio recordings of the therapy sessions will be made, and a random sample of recordings will be checked for treatment fidelity using checklists tailored to the specific treatment.

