### Secondary outcomes

To investigate trauma exposure, comorbidity, experiential avoidance, dissociation, social support, verbal memory and cortisol as predictors and/or moderators of treatment outcome, we will use the Dutch versions of the:

International Trauma Questionnaire (for complex PTSD).^29 30^Moral Injury Outcome Scale (for moral injury after a potentially morally injurious event).^31^The Hospital Anxiety and Depression Scale (for comorbid anxiety and depression).^32^Avoidance Assessment Questionnaire (for experiential avoidance).^33^Personality Inventory for DSM-5-Brief Form-Adult (for maladaptive personality traits).^34^Dissociative Symptoms Scale (for dissociative symptoms).^35 36^Crisis Support Scale (for social support and satisfaction with support).^37^California Verbal Learning Test (in Dutch: Verbal Learning and Memory Test (VLGT); for verbal memory performance).^38 39^MINI International Neuropsychiatric Interview – Simplified for DSM-5 (MINI-S; for the exclusion criteria of current psychotic disorder, severe alcohol or substance use disorder, high suicidal intent with a concrete suicide plan).^40 41^The Life Events Checklist (LEC-5; for PTEs).^42^The Adverse Childhood Events – International Questionnaire (for adverse experiences in childhood).^43^,^45^The Credibility and Expectancy Questionnaire (for patients’ confidence in the treatment and perceived treatment credibility).^46 47^

All these instruments have good psychometric properties. Furthermore, we will assess harms as recommended by the STRONG STAR consortium^48^ and hair cortisol for stress levels at baseline.

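### Therapist inquiry about adverse events follows treatment days, so ascertainment differs by arm, mainly between weeks 7 and 17; any between-arm harms comparison should rest on the common T1–T4 inquiries

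*Protocol article*

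**What the plan says.** Under Adverse events, the protocol article sets two collection channels. The first is tied to treatment: "Therapists will inquire about adverse events at the start of each treatment day". The second is tied to the calendar: "Adverse events will also be monitored at all post-assessments and followed up by the research team". Under Measures, the post-assessments fall at 7 weeks (T1), 17 weeks (T2), 6 months (T3) and 9 months (T4), at the same points in both groups. Under Secondary outcomes the article adds that "we will assess harms as recommended by the STRONG STAR consortium", without giving the instrument or its timing.

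The number of treatment days follows from the two treatment sections.

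- **M-TFT:** "Participants engage in two preparatory sessions once per week, lasting 50 min each"; then a core block "consisting of 5 days of M-TFT delivered over 1 week or 2 weeks"; then "Two 50-minute closing sessions, one in week 5 and one in week 6". On core days, "Each M-TFT day features a 60-minute PE therapy session, a break and a 60 min EMDR session", so two sessions share one treatment day.
- **S-TFT:** "either 12 weekly 60-minute sessions plus a last 80-minute session (13 total sessions) or 16 weekly 50-minute sessions".

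None of the analysis sections describes a comparison of adverse events between arms.

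**The concern.** The randomised arms differ in how many treatment days they have and how these are spread over time. A rule that asks about harms on each treatment day therefore makes the intensity of ascertainment depend on the arm. M-TFT patients stop being asked by a therapist after week 6, while S-TFT patients are asked weekly until week 13 or 16. If some events are forgotten by the next inquiry, fewer will be recorded in M-TFT during that stretch even when the true rates are equal.

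The article says in its Discussion that the trial may affect guideline recommendations on first-line treatment. Readers will look at adverse events by arm whether or not a formal comparison is planned. The article lists several differences between conditions as limitations (therapist rotation, mix of interventions, supervision frequency), but not this one.

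**Working it through.** **Step 1. Treatment days, checked against the stated 800 minutes per arm.**

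- M-TFT: 2×50 + 5×(60+60) + 2×50 = 800 min, on 2 + 5 + 2 = 9 days.
- S-TFT, 13 sessions: 12×60 + 80 = 800 min, on 13 days.
- S-TFT, 16 sessions: 16×50 = 800 min, on 16 days.

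All three schedules reproduce the stated total, so the day counts are sound.

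**Step 2. Number of inquiries.**

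| | M-TFT | S-TFT (13) | S-TFT (16) |
|---|---|---|---|
| Therapist inquiries | 9 | 13 | 16 |
| Plus T1–T4 | 13 | 17 | 20 |
| M-TFT:S-TFT ratio, therapist only | – | 9/13 = 0.69 | 9/16 = 0.56 |
| M-TFT:S-TFT ratio, all inquiries | – | 13/17 = 0.76 | 13/20 = 0.65 |

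**Step 3. Where the difference arises** (assuming the first session is in week 1).

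- Up to week 7: 9 therapist inquiries in M-TFT against about 7 in S-TFT.
- From T1 (week 7) to T2 (week 17): none in M-TFT, weekly until week 13 or 16 in S-TFT.
- After T2: only T3 and T4, the same in both arms.

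**Step 4. Possible effect on recorded counts with no true difference.** Assumptions: a constant and equal event rate over 39 weeks (9 months), full capture in weeks covered by therapist contact, and a proportion r recalled at the next post-assessment in all other weeks. The documents give no value for r, so a range is shown. Captured weeks are:

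- M-TFT: 6 + 33r
- S-TFT, 16 sessions: 16 + 23r
- S-TFT, 13 sessions: 13 + 26r

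| r | M-TFT | S-TFT (16) | S-TFT (13) | M-TFT:S-TFT ratio |
|---|---|---|---|---|
| 0.25 | 14.25 | 21.75 | 19.5 | 0.66–0.73 |
| 0.50 | 22.5 | 27.5 | 26 | 0.82–0.87 |
| 0.75 | 30.75 | 33.25 | 32.5 | 0.92–0.95 |
| 1.00 | 39 | 39 | 39 | 1.00 |

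**Step 5. A second recall model.** Here each event is reported at the next inquiry of either kind with probability exp(−delay/τ). Captured weeks are the sum of τ(1 − exp(−L/τ)) over the gaps L between inquiries. The values of τ are again assumptions. Over 39 weeks the M-TFT:S-TFT ratio is 0.98 for τ = 52 weeks, 0.91–0.93 for 13 weeks, 0.77–0.82 for 4 weeks and 0.58–0.69 for 1 week. With no forgetting it is 1.00. Up to week 7 alone it is 0.96–1.03 across all values of τ, which confirms that the imbalance comes later.

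**The case against.** The strongest reply is that the biased comparison is not in the document. The article does not say that counts from the two channels will be pooled or that adverse events will be compared between arms. How harms are tabulated is commonly left to the full protocol or the analysis plan, which are not shown. This stands: a reader might infer that the planned analysis will make massed treatment look safer, and the article does not support that. What remains is the stated collection rule. It is unequal by design, and no later analysis can recover an event that was never elicited.

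A second reply is that the common channel already exists at T1–T4. This is correct. It shrinks the imbalance without removing it, because those inquiries are added to unequal therapist inquiries. It also makes the remedy easy.

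Two stronger readings are tempting and should be resisted.

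- **A larger bias.** Stopping the Step 4 calculation at week 17 gives, at r = 0.5, (6 + 5.5)/(16 + 0.5) = 0.70 or (6 + 5.5)/(13 + 2) = 0.77. Monitoring runs to 9 months, and weeks 17–39 are observed identically in both arms, so this exaggerates the effect on total counts.
- **The weeks after the intensive block as the least observed.** M-TFT patients are seen in weeks 5 and 6 and at T1 in week 7. Their T1–T2 gap is about 10 weeks, whereas the longest gap, T3–T4, is about 13 weeks and is equal in both arms.

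Finally, the consortium-recommended harms assessment may add a further symmetric channel. Its content cannot be seen here, so it can neither be credited nor dismissed.

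**Conclusion.** The point holds in a limited form. The stated schedule gives unequal ascertainment by arm, concentrated between weeks 7 and 17. If events from both sources are summarised together by arm, the totals will tend to favour M-TFT unless recall is complete.

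The inquiry counts follow directly from the article. The size of any bias does not: it rests on assumed recall, equal and constant true rates, sessions starting in week 1, and full capture in weeks with therapist contact. It is close to nil for events remembered for months, such as serious ones, and largest for mild or transient events. The priority is minor. The case for acting is that the change costs little and recruitment is planned to run until July 2027.

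**What to change.** 1. Record the source of each adverse event (therapist inquiry or post-assessment) on the adverse-event form, if it is not already there.
2. State that any between-arm comparison of harms uses events elicited at T1, T2, T3 and T4, with the same questions and a 'since last assessment' window in both arms, asked whether or not the event has already been told to a therapist.
3. Report therapist-elicited events separately by arm, as descriptive safety data.

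The treatment-day inquiry stays as it is. The cost is one sentence in the protocol or analysis plan and one form field, using contacts already planned. The downside is that the comparison uses fewer events and relies on recall over longer intervals, equally in both arms. For participants already enrolled, the source can be assigned only if existing records show it.

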### Data management and monitoring

Data will be pseudonymised as much as possible and stored under secure conditions with restricted access, available to the research team only in compliance with current data storage protocols. All electronic data will be collected in a software solution (Castor EDC) and stored on a secured network with servers within the EU. Data will be stored for 15 years after study completion. The metadata will be placed in a repository. The dataset can be delivered on request for meta-analyses and aggregated analyses based on the abovementioned stipulations and will be anonymised by removing identifiable information. If participants wish to stop participating in the study, data previously collected will be stored for up to 15 years and used for initial analyses.

Because this study does not investigate a product, the study was exempted from involving a data safety monitoring board. During the data collection phase, an independent monitor will perform monitoring at least twice a year.

### Dissemination

The trial’s results will be communicated in several ways. First, several peer-reviewed publications will be published in an Open Access format, with a predetermined range and order of authors. Because of the sensitive nature of the data, patients are asked for optional consent to share their anonymised data with other research projects. Data from the patients who give this optional consent are available from the corresponding author via email on reasonable request and with the requirement that the submitted research proposal and data access agreement must first be approved by ARQ Centrum’45 and Rijksuniversiteit Groningen who are joint owners of the data. Results will be presented in meetings of professional associations. In addition, factsheets and information materials on massed versus spaced treatment will be made available for therapists, referring professionals, patients and family members/caregivers, health insurance companies and employers.

### Patient and public involvement

Multiple patients were involved in the design of the study. A patient panel provides feedback throughout the data collection phase on a variety of aspects, such as feasibility and recruitment strategies.

## Discussion

The main goal of this multicentre, parallel, single blinded, non-inferiority RCT is to investigate whether M-TFT in comparison with S-TFT is non-inferior in reducing PTSD symptoms in patients seeking first-time treatment for PTSD, as well as more cost-effective. Although S-TFT is effective, it may be unnecessarily prolonged and consequently relatively cost-ineffective, especially in multiply traumatised individuals who are employed. M-TFT might lower costs from a societal perspective while retaining effectiveness. Should M-TFT prove to be non-inferior to and/or more cost-effective than S-TFT, it might impact both Dutch and international guidelines for first-line PTSD treatment.^8 9^ Regarding the type of massed treatment, we aim to investigate the effectiveness of combining PE and EMDR. This approach, widely used in the Netherlands and with proven preliminary effectiveness in uncontrolled studies (e.g., a study by Zoet *et al.*^51^), has yet to be compared against an active control group. This RCT is particularly well-designed to assess its effectiveness.

The secondary goal of this study is to investigate differential effects on drop-out and identify predictors and moderators of M-TFT and S-TFT. Several previous RCTs have found that M-TFT results in lower treatment drop-out than S-TFT.^52^ With this RCT, we would like to test whether these findings can be replicated. Qualitative interviews with patients will be performed to further contribute to the identification of factors and subpopulations for whom M-TFT might be especially effective.

### Strengths

There are several strengths of this study. First, by studying a massed format in a previously unstudied PTSD population (i.e., those without prior treatment and still employed), we can test whether previous findings of both clinical and cost-effectiveness may be replicated in this new population. Second, the variety of centres throughout the Netherlands ensures a diverse population affected by a broad range of PTE types, which increases the generalisability of findings. Third, by using multiple types of treatment interventions, the control condition strongly resembles standard clinical care. The RCT contains elements of pragmatic trials, therefore introducing more variation between conditions, but also enabling a more valid comparison.

### Limitations

The study design also has several limitations. First, multiple differences between conditions exist. Therapist rotation is only applied in M-TFT. Because therapist rotation is not associated with a significant difference in the therapeutic relationship,^19^ it probably will not explain potential differences in clinical effectiveness. Second, although external validity is increased by allowing multiple treatment interventions, this introduces another confounding variable. However, the treatment interventions share many elements, including psychoeducation, imaginal exposure, emotional processing, cognitive restructuring and/or meaning-making,^20^ keeping variation limited. Third, supervision frequency is higher in M-TFT than S-TFT. This difference in supervision is proportionate to the increased treatment session frequency, affording therapists in both conditions two opportunities per patient.

## Ethics and dissemination

The study procedures were reviewed and approved by the Medical Ethics Review Board of the Amsterdam University Medical Centre (NL86057.018.24), and the protocol (version 3; 16-07-2024) is preregistered in Overview of Medical Research in the Netherlands (OMON; trial register number 56960) and ClinicalTrials.gov (NCT06700590). The sponsor has insurance for compensation to those who suffer harm from trial participation.
